### Statistical Analysis of Neuroimaging Results

The ALFF values and FC between the Tai Chi group and the health education group will be compared using independent samples *t* tests. A 2-sample *t* test will be used to compare the ALFF values between the 2 groups. Pre- and postintervention data within groups will be compared using paired *t* tests. After the ALFF analysis, the maximum peak coordinates of different brain regions will be selected, and the cluster at the peak coordinates will be considered the region of interest. Differences in FC of the region of interest with the whole brain will be calculated. Correlation analyses will be conducted using Pearson correlation coefficients based on clinical and fMRI imaging data. Missing data will be processed using the multiple imputation method.

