Functional connectivity (FC) refers to the degree of correlation between BOLD signal time series in different brain areas over time. Each voxel in a brain region contains a time series that represents the level of signal change associated with that region over time. Brain areas with significant differences in ALFF are selected as regions of interest for whole-brain FC analysis to assess changes in brain network connectivity. Changes in the time series can identify brain areas that are functionally coordinated and positively correlated with the BOLD signal, while areas negatively correlated are considered antagonistic. The most common form of FC is voxel based (seed-based FC). This process involves selecting a seed point and calculating the correlation between the BOLD signal of the seed point and that of all other voxels throughout the brain.

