### Statistical Analysis

All statistical analyses and processing will be independently performed by a researcher who did not participate in the treatment or scale assessments during the process. The Statistical Package for the Social Sciences version 20.0 (IBM Corporation) will be used for statistical analysis. Quantitative data with a normal distribution will be described as mean (SD). For quantitative data with a nonnormal distribution and outcome indicators, the rank-sum test will be used. A *P* value of <.05 indicates a statistically significant difference.

For the neuropsychological test outcome indicators, ANT, and N-Back test behavioral metrics, a 2 (group: Tai Chi group, education group) × 2 (time: pretest, posttest) repeated measures ANOVA will be used. For cases not meeting the sphericity test, the Greenhouse-Geisser method will be applied to correct the statistical data (degrees of freedom and *P* value), and Bonferroni correction will be applied for post hoc comparisons. All statistical inferences will be 2-tailed, with the level of significance set at α=.05. A *P* value of <.05 indicates statistically significant differences.

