This study uses more precise and scientific neuropsychological experimental paradigms, such as the ANT and N-Back, to assess specific domains of cognitive impairments in CFS. It provides objective and accurate data to support the assessment of cognitive impairments in CFS. This approach offers a theoretical basis for the early clinical diagnosis and intervention of cognitive function impairments in patients with CFS, offering significant guidance.

Resting-state fMRI studies are essential for elucidating the intrinsic functional organization of the brain and can enhance our understanding of brain functional changes in CFS and its treatment. Neuroimaging scans can reveal changes in brain activation and FC in patients with CFS after Tai Chi interventions, providing clear, effective, and direct evidence. Previous fMRI studies have found brain functional changes or metabolic abnormalities in areas such as the prefrontal cortex, posterior cingulate cortex, parieto-occipital cortex, hippocampus, parahippocampal gyrus, and precuneus in patients with CFS. These changes in the central nervous system may serve as a pathological basis for the physical fatigue and cognitive impairments observed in patients with CFS [39,40].

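### The imaging analysis tests pre-post change only within each arm and states no between-arm comparison of change or baseline adjustment; the meaning of its .05 threshold for brain maps should also be stated.

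*Protocol article*

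**What the plan says.** Methods, Statistical Analysis of Neuroimaging Results, sets out the imaging tests. ALFF and FC are compared between the Tai Chi and health education groups by independent samples t tests, and the section repeats that a two-sample t "test will be used to compare the ALFF values between the 2 groups". Change over time has its own sentence: "Pre- and postintervention data within groups will be compared using paired" t tests. Neither sentence mentions a between-arm comparison of change or an adjustment for the baseline scan. The section does not say which visit the compared ALFF values come from.

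The seeds follow from the ALFF step. Preliminary Processing of fMRI Data says "Brain areas with significant differences in ALFF are selected as regions of interest for whole-brain FC analysis". The neuroimaging section adds that "the maximum peak coordinates of different brain regions will be selected, and the cluster at the peak coordinates will be considered the region of interest". FC from those regions is then examined over the whole brain, and imaging measures are correlated with clinical data.

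Table 1 (Outcome Measure Assessment) schedules ALFF and FC at baseline and postintervention without distinction by arm. The general Statistical Analysis section plans a group × time repeated measures ANOVA for the cognitive tests. It sets the only error rate in the article: "All statistical inferences will be 2-tailed, with the level of significance set at α=.05". Its only multiplicity adjustment belongs to that ANOVA: "Bonferroni correction will be applied for post hoc comparisons". No voxel or cluster threshold is given for the maps.

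**The concern.** The purpose of randomising is to compare arms. For a measure scanned before and after treatment, the natural treatment contrast is the difference between arms in change, or in the final value given baseline. The neuroimaging section states neither. The only tests of change it names are within a single arm, where time, repeat scanning and regression to the mean can all produce a difference with no treatment effect. A reader shown a significant pre-post map in the Tai Chi arm and a non-significant one in the control arm is likely to take that as an effect of Tai Chi, and the plan gives no direct test to set against it.

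The threshold is a second, smaller matter. ALFF is computed for each voxel. If the one stated error rate were applied to each voxel without correction, chance clusters would appear, and the seed rule would carry them into a second whole-brain search.

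What is at stake is a secondary outcome, since the Abstract lists MRI among the secondary measures. The primary fatigue outcome is unaffected.

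**Working it through.** **Sample size used below.** The article gives no error rate for imaging to reproduce, so its sample size is the only design figure that can be checked. From Sample Size Calculation: means 4.80 (SD 2.11) and 7.13 (SD 3.29). Pooled SD = √[(2.11² + 3.29²)/2] = 2.764; d = 2.33/2.764 = 0.843. The exact two-sample t calculation at two-sided .05 and power .80 gives 23.09, so 24 per arm, and 24/0.8 = 30. The stated 24 and 30 reproduce. I use 24 per arm as the number left after 20% dropout.

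**Within-arm tests against a direct test.** Assumptions, not in the article: one imaging measure, equal true change δ in both arms (in baseline SD units), equal SD at both visits, pre-post correlation r = .5.

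- SD of change = √[2(1 − r)] = √[2 × 0.5] = 1.
- Each paired t test has 23 df and noncentrality δ√24; call its probability of significance p.
- The arms are independent, so the probability that exactly one is significant is 2p(1 − p). Its ceiling is 50%, at p = .5.

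| δ (SD) | p | exactly one arm significant |
|---|---|---|
| 0 | .050 | 9.5% |
| 0.2 | .156 | 26% |
| 0.4 | .467 | 50% |
| 0.6 | .804 | 32% |
| 0.8 | .963 | 7% |

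For δ = 0.4: noncentrality 0.4 × 4.899 = 1.96, p = .467, and 2 × .467 × .533 = .498. A simulation of 20,000 trials at this setting gave 49.5%, and 5.0% for the direct between-arm t test on change. The direct test keeps its 5% whatever the common change, because δ cancels between arms.

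**What baseline adjustment adds.** In units of the outcome variance, the unadjusted postintervention comparison has variance factor 1, change scores 2(1 − r), and baseline adjustment 1 − r². At r = .5 these are 1, 1 and 0.75. Adjustment therefore cuts the variance by a quarter on this assumption; at r = .3 the factor is 0.91 and at r = .7 it is 0.51.

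**The threshold, if .05 were applied per voxel without correction.** Voxel size after resampling is 3 × 3 × 3 = 27 mm³ (Preliminary Processing of fMRI Data). Brain volume is assumed to be 1.2 to 1.9 litres.

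- Voxels: 1,200,000/27 = 44,444 to 1,900,000/27 = 70,370.
- Expected false-positive voxels per null map: 0.05 × 44,444 = 2,222 to 0.05 × 70,370 = 3,519.
- Simulated null maps (59,400 voxels, 30 against 30, 25 maps per setting, assumed smoothness 4, 8 and 12 mm FWHM): every map contained false clusters, on average about 1,935, 370 and 125 per map.
- A voxel threshold of P<.001 alone is not enough. At 8 mm all 25 null maps still had false voxels, and 56% had a cluster of 10 or more voxels.

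**The seed step.** Suppose a null region is chosen because its ALFF difference reached .05. The chance that a null FC test from it is also significant stays at about 5% if ALFF and FC are uncorrelated across participants. It is about 10%, 19% and 33% at assumed correlations of .3, .5 and .7.

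**The case against.** The strongest reply is that the article plans between-group tests first and the paired tests are additional. A comparison of postintervention values between randomised arms is valid without adjustment, and nowhere does the article say that significance in one arm only will be read as a treatment effect. This largely stands. The 7% to 50% range describes a reading that the plan leaves open, not a decision rule it adopts, and it models one measure rather than a map. Still, change is tested only within arms, the visit for the between-arm comparison is not named, and the baseline scan is not used in any stated treatment comparison.

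A reader might also infer that the maps will be tested with no multiplicity control and that false findings are near certain. The article does not support that. It states no voxel or cluster threshold of either kind; a level of .05 is compatible with a corrected .05; and the correction method may sit in the full protocol or analysis plan, which is not shown.

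Nor is seeding FC from ALFF clusters circular in itself. FC is a different statistic, and its error rate rises only if the two measures are correlated across participants. Fixing seeds in advance, for instance in the regions that the Discussion lists ("prefrontal cortex, posterior cingulate cortex, parieto-occipital cortex, hippocampus, parahippocampal gyrus, and precuneus"), is a trade-off rather than a correction.

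Finally, the limitations in the Discussion already call the neuroimaging exploratory with a limited sample. That lowers the weight of the whole point. It sits badly, however, with the later statement in the Discussion that the trial will objectively show efficacy by means of fMRI.

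**Conclusion.** The point holds for the treatment contrast. As written, the imaging section offers unadjusted between-arm t tests and within-arm tests of change, and states no between-arm test of change or baseline adjustment, although the scans to do so are scheduled in both arms and the cognitive tests already get a group × time analysis. Relying on the paired tests would give a one-arm-only result in about 7% to 50% of trials with equal true change, against 5% for the direct test. This rests on assumed changes of 0 to 0.8 SD, r = .5 and 24 per arm; the upper end is the mathematical ceiling, reached near 0.4 SD.

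The threshold point is conditional. The figure of 2,200 to 3,500 false voxels applies only if .05 is used per voxel without correction and the brain mask is 1.2 to 1.9 litres. What can be asked for is a statement of what .05 refers to. The matter concerns a secondary outcome that the article itself describes as exploratory.

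**What to change.** 1. In the neuroimaging section, name the treatment comparison as the between-arm difference in postintervention ALFF and FC adjusted for the baseline map, or the between-arm comparison of post-minus-pre maps. Keep the within-arm paired tests as description only. The cost is slightly more analysis work; no new data are needed, and the article says that analysis has not started.
2. State that .05 for the maps is a cluster-level family-wise rate with a voxel-forming threshold of P<.001. The cost is that fewer clusters will reach significance.
3. Report the seed-based FC results and the clinical correlations as exploratory, in line with the limitations paragraph, and tone down the Discussion's claim that fMRI will objectively demonstrate efficacy. This costs wording only.

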### Ethical Considerations

This study follows the Declaration of Helsinki (as revised in 2013) and the International Ethical Guidelines for Biomedical Research Involving Human Subjects (Articles 37 and 38). The study protocol and consent forms have been approved by the Shanghai Clinical Research Ethics Committee (approval number SECCR2024-22-01). They were registered on March 26, 2024, in the Clinical Trial Registry (a World Health Organization International Clinical Trials Registry Platform [WHO ICTRP] member) under registration number ChiCTR2400082268.

All participants will be fully informed of the inclusion and exclusion criteria for this study before the trial begins. They will sign informed consent forms before the trial and be informed that they have the right to withdraw from the trial at any time. Recruitment and randomization will be conducted transparently. If changes occur in our research protocol, a written application will be submitted to the research ethics committee. The committee members will decide whether it is necessary to modify the protocol. After the clinical study is completed, a study completion report will be submitted and published in academic journals.

## Results

Participant recruitment commenced in April 2024. All interventions and concurrent data collection will be completed by October 2025. The 4-week postintervention follow-up assessments will be finalized by the end of October 2025. Data management is currently ongoing, and statistical analysis has not yet been performed.

## Discussion

To the best of our knowledge, this study is the first to explore the effects of Tai Chi on CFS from a cognitive functional perspective. To validate the specific role of Tai Chi in CFS treatment, this study aims to evaluate the impact of Tai Chi on fatigue, cognitive functions, and changes in brain function using different clinical scales, psychological experimental paradigms, and neuroimaging scans. Currently, it is widely accepted in the academic community that CFS can cause cognitive impairments. However, some reports occasionally yield inconsistent results [34,35], possibly because early mild cognitive impairments may not be fully detected by conventional neuropsychological scales and can easily be overshadowed by other clinical symptoms. In most studies, subitems measuring cognitive functions, such as attention and memory, are typically included in the composite scores of scales for other cognitive domains or in overall cognitive assessment paradigms. Moreover, due to the strong subjectivity of scale assessments and the low sensitivity of indicators, there are certain limitations. With the use of various cognitive tasks and different methods of assessing cognitive functions, direct comparisons are not feasible, leaving a lack of more direct evidence for assessing cognitive functions in patients with CFS. Therefore, there is an urgent need to apply more precise and scientific neuropsychological experimental paradigms to assess specific cognitive domains, providing objective and accurate data to support the assessment of cognitive impairments in CFS.

Togo [36] showed that the ANT has clinical value for assessing the cognitive functions of patients with CFS. Some scholars have proposed using continuous attention assessment as a reliable biomarker for diagnosing CFS [37]. Nevertheless, there is still a lack of comprehensive ANT paradigm evaluations and analyses of attention network functions in patients with CFS. The N-Back test is a commonly used paradigm in cognitive psychology for assessing working memory capacity [38], and the N-Back task paradigm, a continuous processing operation task, is one of the most widely used experimental paradigms in working memory brain imaging studies.

This study uses more precise and scientific neuropsychological experimental paradigms, such as the ANT and N-Back, to assess specific domains of cognitive impairments in CFS. It provides objective and accurate data to support the assessment of cognitive impairments in CFS. This approach offers a theoretical basis for the early clinical diagnosis and intervention of cognitive function impairments in patients with CFS, offering significant guidance.

Resting-state fMRI studies are essential for elucidating the intrinsic functional organization of the brain and can enhance our understanding of brain functional changes in CFS and its treatment. Neuroimaging scans can reveal changes in brain activation and FC in patients with CFS after Tai Chi interventions, providing clear, effective, and direct evidence. Previous fMRI studies have found brain functional changes or metabolic abnormalities in areas such as the prefrontal cortex, posterior cingulate cortex, parieto-occipital cortex, hippocampus, parahippocampal gyrus, and precuneus in patients with CFS. These changes in the central nervous system may serve as a pathological basis for the physical fatigue and cognitive impairments observed in patients with CFS [39,40].

The academic community has conducted clinical research on mind-body exercise interventions for CFS from various perspectives, yielding a wealth of effective research outcomes. Tai Chi emphasizes the unity of form and spirit, practiced with the guidance of mind over energy. It stresses the coordination of body and mind, advocating stillness and emphasizing nourishment. It can improve insomnia and fatigue symptoms in patients with CFS without toxic side effects. A meta-analysis showed that Tai Chi can improve fatigue more effectively than traditional therapies and has a positive effect on cancer-related fatigue [41]. Kuangshi et al [42] recruited 21 patients with CFS, with 19 in the control group, implementing a 4-week 24-form Tai Chi training and conducting functional brain MRI. Results showed that, before practicing Tai Chi, the experimental group exhibited significantly weakened FC in the default mode network, compared with the control group, in regions including the left superior temporal gyrus and the left dorsolateral prefrontal cortex. Meanwhile, significantly enhanced FC was observed in the right lateral temporal lobe. Therefore, Tai Chi has a characteristic modulatory effect on abnormal activity in the default mode network of patients with CFS .

Kuangshi et al [43] showed that, after practicing Tai Chi, the experimental group exhibited significantly reduced functional ALFF values in brain regions including the left orbitofrontal/cortical pole, right anterior cingulate gyrus, and right lateral temporal lobe. However, significantly increased functional ALFF values were observed in the left sensorimotor cortex and the right visual cortex. Therefore, Tai Chi exercise can improve fatigue and sleep in patients with CFS, enhancing their quality of life, possibly due to its specific effect on the brain’s sensorimotor cortex, left frontal lobe, right lateral temporal lobe, anterior cingulate gyrus, and visual cortex. This research provides biomarkers for subsequent studies and imaging support for the central mechanism of Tai Chi. However, as an exploratory study with a small sample size, it does not include groups practicing aerobic exercise or other interventions, which would help determine the specificity of the Tai Chi intervention.

Wu et al [44] designed a longitudinal trial with Tai Chi as the intervention therapy, using the FCs of the whole brain as exploratory variables to detect abnormalities in the brain’s connectivity structure in patients with CFS and explore changes during Tai Chi exercise. Our study explored the impact of Tai Chi on brain FC in CFS. Results showed that Tai Chi could improve fatigue, sleep quality, and physical health status in patients with CFS by enhancing the FCs within the left frontoparietal network and default mode network [42].

The results of this trial can evaluate the efficacy of Tai Chi in treating fatigue symptoms and cognitive impairments in patients with CFS by assessing changes in brain activation, ANT and N-Back results, and related clinical scale outcomes.

Despite the promising hypothesis of this study, it also has some notable limitations. First, the screening for inclusion criteria is solely based on self-assessment scales without the use of specialized psychometric testing equipment, which may lead to less stringent inclusion of patients with CFS. However, by limiting participants’ ages to 18-60 years, the likelihood of chronic fatigue caused by medical and psychiatric conditions is reduced. Thus, the study results cannot be generalized to other populations. Second, in this study, the intervention is a nonpharmacological treatment, which cannot be ideally implemented according to double-blind standards. Ideally, each participant should be blinded to the trial; however, this is challenging to achieve in nonpharmacological trials. Hence, bias may be inevitable. However, to ensure the authenticity of the experimental data and reduce biases during the experiment, we will rigorously randomize participants and ensure that the interveners, assessors, and statisticians remain blind to each other. Additionally, the neuroimaging study in this trial is only at an exploratory stage with a limited sample size. In future research, increasing the sample size could provide more persuasive evidence. Finally, this trial only conducted a 4-week follow-up. Therefore, the follow-up period should be extended to validate the long-term clinical outcomes and potential effects of Tai Chi.

Furthermore, this study was designed as a pilot randomized controlled trial, with the primary aim of assessing the feasibility and preliminary efficacy of Tai Chi therapy in patients with CFS. The relatively small sample size limits the statistical power and generalizability of the results; therefore, all findings should be interpreted with caution. The outcomes of this pilot study will help inform the design and methodology of future large-scale, multicenter trials.

Despite the limitations mentioned, this study still possesses several advantages. Compared with other treatment methods, such as medication and psychological counseling, Tai Chi offers significant benefits for patients with CFS. It is easy to learn, not restricted by time or space, and can be practiced independently for therapeutic purposes. Moreover, this is the first study to investigate Tai Chi intervention for cognitive impairments in CFS. More importantly, it will objectively demonstrate the efficacy of Tai Chi in addressing cognitive impairments in CFS using precise, sensitive computerized neuropsychological experimental paradigms and high-spatial-resolution fMRI technology. Finally, the use of posters and social platforms for recruitment aims to include individuals from various social strata, thereby enhancing the representativeness of the sample.

In conclusion, this protocol outlines a rigorous, well-structured pilot randomized controlled trial designed to evaluate the preliminary efficacy and safety of Tai Chi for cognitive impairments in CFS.

While the findings may not be definitive, they will provide important initial evidence and contribute to the foundation for future larger-scale studies.

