**Methods:**

We will conduct a randomized, analyst-blinded, parallel-controlled trial with a 12-week intervention period and a 4-week follow-up. Enrolled patients will be randomly assigned to either the Tai Chi group (30 patients) or the health education group (30 patients). The Tai Chi group will receive the 24-style simplified Tai Chi intervention, while the control group will receive a health education intervention. Following the 12-week intervention, a 4-week follow-up will be conducted. The Tai Chi group will train 3 times per week, consisting of 2 in-person sessions at the Physical Education Center of Shanghai University of Traditional Chinese Medicine and 1 self-directed session guided online by an instructor. The primary outcome measure is the 20-item Multi-Dimensional Fatigue Inventory (MFI-20). The secondary outcome measures include the Montreal Cognitive Assessment (MoCA), Pittsburgh Sleep Quality Index (PSQI), Attention Network Test (ANT), working memory performance (N-Back task), and magnetic resonance imaging.

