**Conclusions:**

As a pilot trial, the findings of this study will provide preliminary clinical evidence on the role of Tai Chi in improving cognitive function in patients with CFS and will serve as a foundation for designing future large-scale trials.

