### Secondary Outcome Measures

#### MoCA

The MoCA scale is used to assess general cognitive status and overcomes the low sensitivity of other cognitive assessment tools to cognitive impairment. It is one of the most widely used cognitive assessment tools in clinical practice and effectively screens for cognitive dysfunction caused by various diseases, especially with high sensitivity in the early stages. It covers a wide range of cognitive domains, including orientation, attention, language, visuospatial function, memory, and executive functions. The total score is 30, with a score of 26 or higher considered normal. Scores are slightly adjusted based on educational level; for example, participants with less than 12 years of education receive an additional point added to their final MoCA score.

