In the experimental condition, participants are required to place their hands on the keyboard and focus their eyes on the fixation point in the center of the computer monitor. They must make a fast and accurate autonomous response based on the direction of the target stimulus. Specifically, if the central arrow of the target stimulus points left, participants are instructed to press the “F” key. If the central arrow points right, they should press the “J” key. The software automatically records the participant’s accuracy and reaction time. The task begins with 24 practice trials, followed by the formal experiment, which is divided into 3 blocks, each containing 96 trials. Participants are allowed to rest appropriately between blocks and can start the next block by pressing the space bar on the keyboard. The distribution of cue stimuli and target stimuli is balanced to ensure equal representation across trial types. The total duration of the task is approximately 30 minutes. The behavioral metrics include accuracy rate (higher is better), reaction time (faster is better), alerting score (no-cue reaction time [RT] to neutral-cue RT), orienting score (neutral-cue RT to spatial-cue RT), and conflict score (incongruent RT to congruent RT).

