#### N-Back Test

This study uses the N-Back task paradigm to assess working memory, one of the classic experimental approaches for evaluating this cognitive function. The task is implemented using E-Prime 3.0 software and is performed on a computer with a keyboard. It presents stimuli and records participants’ reaction times and accuracy rates across all trials. During the test, participants are required to sit in front of the computer screen, maintaining a horizontal distance of 60 cm. The index fingers of the participant’s left and right hands should lightly touch the F and J keys on the keyboard, ready to respond by pressing a key when a letter appears. The N-Back paradigm includes 3 levels of memory load (0=back, 1=back, and 2=back tasks), with stimuli consisting of the letters A, B, C, D, E, and F against a black screen background with white letters. At the start of the experiment, a “+” is first displayed for 500 ms, followed by the random presentation of English letters. Each stimulus is presented for 500 ms, with an interstimulus interval of 2000 ms (blank screen). If no response is made within 2000 ms, the next stimulus is automatically presented. After each block, a prompt message saying, “Please rest for a moment; press the space bar to continue” appears. In the 0=back task, participants are instructed to compare the current letter with “X” and press the F key if they are the same or the J key if they are different. In the 1=back task, starting from the second letter, participants are instructed to determine whether the current letter is the same as the previous letter, pressing the F key if they are the same or the J key if they are different. In the 2=back task, starting from the third letter, participants are instructed to determine whether the current letter is the same as the letter 2 positions back, pressing the F key if they are the same or the J key if they are different. Participants are required to respond both quickly and accurately. The task includes 60 practice trials, followed by the formal experiment, which consists of 9 blocks, each with 30 trials (15 targets and 15 nontargets). Each memory load level includes 3 blocks, with the 0=back, 1=back, and 2=back tasks completed in sequence. Each task type involves a total of 90 stimuli (30 × 3), with a target-to-nontarget ratio of 1:1, presented in a pseudorandom order. The behavioral metrics include reaction time and accuracy rate.

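### The Discussion promises a demonstration of cognitive efficacy, but cognition rests on 8 to 12 unranked secondary measures, each tested at two-sided .05 in a 60-person pilot

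*Protocol article*

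**What the plan says.** The Abstract (Methods) states: "The primary outcome measure is the 20-item Multi-Dimensional Fatigue Inventory (MFI-20"). The Sample Size Calculation uses that scale alone. The cognitive measures appear in the secondary list, with no order of importance: "The secondary outcome measures include the Montreal Cognitive Assessment (MoCA), Pittsburgh Sleep Quality Index (PSQI), Attention Network Test (ANT), working memory performance (N-Back task").

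- **MoCA section:** "The MoCA scale is used to assess general cognitive status", reported as one total score.
- **ANT section:** "The behavioral metrics include accuracy rate (higher is better), reaction time (faster is better), alerting score", followed by an orienting and a conflict score. A direction of benefit is given for accuracy and reaction time, and for none of the three network scores.
- **N-Back Test section:** "The behavioral metrics include reaction time and accuracy rate". The task has three memory loads. The section does not say whether each load is tested separately.
- **Statistical Analysis section:** a group by time repeated measures ANOVA for the neuropsychological, ANT and N-Back measures, a two-tailed .05 level for all inferences, and Bonferroni for post hoc comparisons. No correction across measures is described.

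The Abstract (Conclusions) expects "preliminary clinical evidence on the role of Tai Chi in improving cognitive function in patients with CFS". The Discussion goes further: "it will objectively demonstrate the efficacy of Tai Chi in addressing cognitive impairments in CFS". Close to that sentence it also calls the trial a pilot, asks for cautious reading because the sample is small, and allows that the findings may not settle the question.

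**The concern.** The quoted sentence makes a confirmatory promise about cognition. The trial's one protected endpoint is a fatigue scale, and nothing in the article says which cognitive measure would have to be positive for the promise to be kept. The Discussion argues that "early mild cognitive impairments may not be fully detected by conventional neuropsychological scales" and therefore leans on the ANT and N-Back tasks, which are the instruments with the most separate metrics. With many metrics at .05 and no lead measure, a chance result somewhere in the cognitive set is likely enough that it could be written up as the announced demonstration. For the alerting, orienting and conflict scores, the reading of a shift as better or worse could be settled after the data are seen. The pilot is meant to inform larger trials, so a chance finding could set their cognitive endpoint.

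**Working it through.** **The plan's own figure.** d = (7.13 − 4.80) / √((2.11² + 3.29²)/2) = 2.33 / 2.764 = 0.843. A two-sided t test at .05 with 80% power needs 23.1 per group, rounded up to 24. Allowing for 20% dropout, 24/0.80 = 30 per group, 60 in total. This reproduces, and it concerns MFI-20 only. The article gives no error rate for the cognitive set, so the rest is derived.

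**Count of cognitive measures, one between-group test each at one visit.**
- MoCA: 1 (total score).
- ANT: 5 (accuracy, reaction time, alerting, orienting, conflict).
- N-Back: 2 with loads pooled, or 2 × 3 = 6 with each load tested.
- Total: 1 + 5 + 2 = 8, or 1 + 5 + 6 = 12. Imaging measures are not counted.

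**Chance of at least one significant result with no true effect.** Under independence this is 1 − 0.95^m for either direction:
- m = 8: 1 − 0.95^8 = 33.7%
- m = 12: 1 − 0.95^12 = 46.0%

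Counting only results in Tai Chi's favour, it is 1 − 0.975^m:
- m = 8: 18.3%
- m = 12: 26.2%

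**Allowing for correlation.** The article gives no correlations, so these are assumed. Test statistics were simulated as equicorrelated normals, X_j = √ρ·Z + √(1−ρ)·E_j, with 400,000 draws and a critical value of 1.96. The ρ = 0 rows are the formulas above.

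| Measures | Assumed ρ | Any significant result | Favouring Tai Chi |
|---|---|---|---|
| 8 | 0 | 33.7% | 18.3% |
| 8 | 0.3 | 30.0% | 15.2% |
| 8 | 0.5 | 25.0% | 12.6% |
| 8 | 0.7 | 19.0% | 9.5% |
| 8 | 0.9 | 12.0% | 6.0% |
| 12 | 0 | 46.0% | 26.2% |
| 12 | 0.3 | 39.8% | 20.2% |
| 12 | 0.5 | 32.0% | 16.0% |
| 12 | 0.7 | 23.2% | 11.6% |
| 12 | 0.9 | 13.5% | 6.7% |
| 1 | n/a | 5% | 2.5% |

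**Undefined direction.** Suppose a significant shift either way in the three ANT network scores could be described as improvement. Those three then count at .05 and the other nine at .025. For 12 independent measures: 1 − 0.975^9 × 0.95^3 = 1 − 0.796 × 0.857 = 31.7%, against 26.2% when the direction is fixed for all.

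**The case against.** Unranked, unadjusted secondary outcomes are ordinary in a 60-person pilot, and ranking them is often left to a statistical analysis plan, which is not shown here. The hedges are real: the Objective and the Abstract's conclusion speak of preliminary efficacy or evidence, and the Discussion itself asks for caution. The quoted sentence sits in a paragraph that lists the study's strengths and is not part of the analysis section. All of this stands, and it rules out three stronger readings.

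- *A reader might infer that no cognitive endpoint is designated.* MoCA, ANT and N-Back are named and described as secondary outcomes. What is absent is one that carries the cognitive conclusion.
- *A reader might infer that one significant metric counts as proof of efficacy under the plan.* No such rule is written. The Statistical Analysis section says only when a difference is called significant.
- *A reader might take 46% as the rate of false claims for Tai Chi.* That figure needs 12 measures, independence and both directions, including results against Tai Chi. The 12 is itself inferred, because separate tests at each N-Back load are not stated. Reaction times from one task will also be correlated.

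The objection does not remove the conflict inside the article. The article states the error level and the reach of the Bonferroni correction itself, and it makes an unhedged claim that these do not support. The caution it asks for is tied to sample size, not to the number of cognitive tests. An unseen analysis plan could rank the measures, but the sentence would still contradict the text around it.

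**Conclusion.** The point holds as a mismatch between one claim and the design. The statement that cognitive efficacy will be demonstrated conflicts with the Discussion's own caveats, and it is out of reach for 8 to 12 unranked secondary measures at two-sided .05. With no true effect, the chance of at least one significant cognitive result is at most 34% to 46%, and about 25% to 32% at a correlation of 0.5. For results favouring Tai Chi among 12 measures it is about 26% under independence and 16% at 0.5, against 2.5% for a single endpoint. It stays above the single-endpoint rate at every correlation tried, up to 0.9. These figures assume one between-group test per measure at one visit, normal test statistics and equal correlations. The missing direction of benefit for the alerting, orienting and conflict scores adds to the problem. The fault lies in wording and designation; it does not call the trial's data or its fatigue analysis into question.

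**What to change.** Before any analysis, which the Results section says has not yet been done:

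1. Either name one cognitive measure, of the sponsor's choice, as the key secondary outcome that alone carries the cognitive conclusion, with its visit and direction of benefit; or declare all cognitive outcomes exploratory.
2. Report the remaining cognitive metrics as estimates with confidence intervals and without efficacy claims.
3. State the direction of benefit for the alerting, orienting and conflict scores, or say that they are not read as benefit or harm.
4. Replace the quoted Discussion sentence with wording fit for a pilot, consistent with the caveats beside it.

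This needs wording changes and no new data. The price is that a positive result on a measure not designated in advance can no longer be claimed as efficacy. Correcting across the whole set would cost more. With 30 per group and 80% power, a two-sample t test detects d = 0.74 for one measure at .05, but only d = 0.99 at .05/12 = .0042.
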